#### Exclusion criteria

We exclude people in case of: a) bipolar disorder any primary psychotic disorder (current and previous), clinically relevant neurological or other somatic illness and/or current alcohol or drug dependency, assessed with the Mini International Neuropsychiatric Interview (MINI [31]); b) high dosage of benzodiazepines (> 2 mg Lorazepam equivalents daily); c) recent electroconvulsive therapy (< 3 months ago); d) previous MBCT/MBSR course and/or extensive meditation experience (e.g. retreats); e) current psychotherapy with a frequency of more than once per three weeks and f) visual hearing or cognitive impairments that impair the completion of self-report questionnaires and interviews.

### Interventions

#### mADM

All study participants are on a stable dose of mADM for at least 6 months prior to enrollment (inclusion criterion). In the mADM group participants continue their use of mADM during the study period of 15 months. After randomization, participants are seen by a study psychiatrist for a review of their mADM. For optimization of mADM, psychiatrists taking part in the study use a protocol based on national [32] and international [33] guidelines, made applicable for the MOMENT study by two experts in pharmacological treatment of MDD ([name]). Switching or augmenting medication is allowed between T0 and T1, and recommendations to manage side effects are provided. Compliance with mADM is measured prospectively during the whole study period using a daily calendar. Participants in the mADM condition are invited to take part in the MBCT training after the study period if they are interested.

#### mADM + MBCT

In the combination group participants are seen by a psychiatrist for a review of their mADM as described above, and are asked to continue their mADM during the study period. In addition, these patients are invited to take part in the MBCT training, a manualized group skills-training program [11]. MBCT is based on the protocol of Mindfulness-Based Stress Reduction (MBSR) which was developed by Jon Kabat-Zinn [34] combined with elements of Cognitive Behavioral Therapy (CBT [35]), turning it into a relapse prevention programme for patients with recurrent depression. The training consists of eight weekly sessions in a group (8 – 15 participants) with a duration of 2.5 hours, plus one day of silent practice between the 6th and 7th session. The silent day, although originally not in the MBCT program, was incorporated following the MBSR protocol [34] to give participants the opportunity to deepen their mindfulness practice. Formal meditation exercises that are part of the program are the body scan, sitting meditation, walking meditation and mindful movement. The program also encourages participants to cultivate awareness of everyday activities, such as eating or taking a shower. Cognitive techniques that are part of the program are education, monitoring and scheduling of activities, identification of negative automatic thoughts and devising a relapse prevention plan. Participants are expected to practice meditation at home for about an hour a day. In addition, participants in the MBCT conditions are invited to take part in three booster sessions every three months during the study period (around 3, 6 and 9 months after MBCT) to enhance their mindfulness practice through peer and teacher support and rehearsal of the key components of MBCT. *Delivery of MBCT and check for competence and adherence.* MBCT courses are provided at 12 different locations in the Netherlands and are led by one or two MBCT teachers per site. MBCT teachers were trained in the study protocol for MBCT during a 3-day training retreat in the beginning of the project, as well as at three subsequent training days every 6 months. Teaching sessions of each (pair of) teacher(s) are videotaped to check treatment integrity. Two tapes per teacher are randomly selected and rated by highly experienced MBCT/MBSR trainers. Competence and adherence are evaluated with the Mindfulness-Based Interventions – Teaching Assessment Criteria [36].

#### *MBCT (with tapering of mADM*)

In the ‘MBCT only’ condition participants are invited to take part in the MBCT course as described above. In addition, they are asked to taper off their mADM from session 7 of the MBCT course onwards. The protocol specifies a tapering scheme lasting 5 weeks for all common ADMs, especially addressing procedures to handle symptoms characteristic for discontinuation [37] (available on request). In case of more exceptional treatments (e.g. lithium addition) withdrawal is based on the shared opinion of the authors of the medication protocol. Clients are seen by a consultant psychiatrist for a minimum of 3 and a maximum of 12 appointments. The first three consultations are scheduled around session 1 (informing and preparing participants), session 7 (initiating withdrawal) and approximately four weeks after session 7 (evaluation of withdrawal). If more guidance is needed, additional appointments can be scheduled. Patients are reassured that they can restart ADM as soon as they suffer a relapse/recurrence, or when withdrawal proves to be unfeasible.

### Outcome measures

Table 1 presents an overview of the outcome measures and the time points of assessments.

**Table 1 T1:** Overview of the measures and corresponding time points

**Measure**	**Target concept**	**T0**	**MBCT**	**T1**	**T2**	**T3**	**T4**	**T5**
SCID-I*	Diagnosis of (recurrent) MDD	●		●	●	●	●	●
IDS-C	Current depressive symptoms	●		●	●	●	●	●
CSRI	(Mental) health service use	●		●	●	●	●	●
MMAS	Medication adherence	●		●	●	●	●	●
RRS	Rumination	●		●				●
LEIDS	Cognitive reactivity	●		●				●
FFMQ	Mindfulness skills	●		●				●
SCS	Self-compassion	●		●				●
WHOQOL-bref	Quality of Life	●		●				●
EQ-5D	Quality of Life	●		●	●	●	●	●
NEO-PI-R	Personality	●						●
MAAS	Daily awareness/attention		●					
I-PANAS-SF	Positive and negative affect		●					
Calendar	Mindfulness and medication adherence, absence from work and health service use Monthly during 15-month study period													

Note. * Module depression (current and/or in the past).

#### Primary outcome measure

*Relapse/recurrence*. Relapse/recurrence is defined as meeting the DSM-IV criteria for a depressive episode at any moment during follow-up assessed by research assistants using the SCID-I. Our follow-up period has a duration of 15 months, therefore both relapse and recurrence can be observed. We refer to ‘relapse’ in case of a depressive episode occurring within 6 months after full remission and we refer to ‘recurrence’ in case of a depressive episode occurring after 6 months of full remission. In general, we refer to ‘relapse/recurrence’ to indicate a depressive episode within the study period. In order to prevent attrition and recall bias, the interviews (either face-to-face or by telephone) are performed at 3 months intervals (T1-T5). At any interview assistants review the previous 3 months since the previous contact. The research assistants received one full day of training to use the SCID-I. Interviews are audio taped to allow second-rating by an independent and blind assessor in cases of actual, borderline or probable relapse/recurrence. Previous studies on inter-rater reliability of the SCID-I have reported Cronbach’s alpha values between 0.61 and 0.80 [38,39].

#### Process data

*Adherence to MBCT and adherence to mADM* is assessed during the entire study period using a calendar on which patients register on a daily basis their adherence to mindfulness exercises formal, informal, or none - and their adherence to mADM - full adherence, partial adherence (e.g. lower dosage than prescribed), or no adherence. This information is combined with the 4-item Morisky Medication Adherence Scale (MMAS [44]) with scores ranging from 0 (perfect adherence) to 4 (low adherence). *Rumination* is measured with the extended version of the Ruminative Response Scale (RRS-EXT [45]). The RRS-EXT enables distinction between ‘reflection’ and ‘brooding’, the former referring to a more adaptive, and the latter to a more maladaptive way of thinking about depression. *Cognitive reactivity* is assessed using the Leiden Index of Depression Sensitivity – Revised (LEIDS-R [46]). This scale consists of six subscales: hopelessness/suicidality, acceptance/coping, aggression, control/perfectionism, risk aversion, and rumination. To examine *mindfulness skills*, we administer the Dutch Five Facet Mindfulness Questionnaire (FFMQ [47]). The scale consists of 39 items divided into the subscales observing, describing, acting with awareness, nonjudging and nonreactivity. *Self- compassion* is measured with the Self Compassion Scale (SCS [48]). The SCS has 26 items measuring three concepts that are related to self-compassion: a) self-kindness versus self-judgment, b) common humanity versus isolation, and c) mindfulness versus over-identification. *Daily attention*. The Mindful Attention Awareness Scale (MAAS [49]) is administered before each MBCT session to assess mindful attention in daily life. *Positive and negative affect* is assessed before each MBCT session using the International Positive and Negative Affect Scale - Short Form (I-PANAS-SF [50]).

#### Cost-effectiveness

The cost-effectiveness evaluation is carried out from a societal perspective considering direct as well as indirect health costs. Data on health and social care utilization are collected prospectively for each individual patient using an adapted version of the Client Service Receipt Inventory (CSRI [51]). The CSRI includes production losses and family support. In addition prospective data are collected using a daily calendar on which participants register a) depression-related absence from work: full absence, partial absence or no absence, and b) any contacts with health care: the type of care and its duration. Unit cost estimates are derived from the national manual for cost prices in the health care sector [52]. Costs of reduced ability to work are estimated using the friction costs method, which results in a more realistic estimate than the human capital approach [53]. Treatment costs of MBCT are calculated using activity-based-costing methods, thus measuring actual resources (time of therapist, time of patients, facilities) used. All unit cost prices are adjusted to 2012 prices. Unit cost estimates are combined with resource utilization data to obtain a net cost per patient over the entire follow-up period. The EuroQoL-5 Dimensions instrument (EQ-5D [54]) is administered to provide utilities. The EQ-5D consists of 5 dimensions: mobility, self-care, daily activities, pain/discomfort and anxiety/depression. In addition, it contains a Visual Analogue Scale to determine Quality Adjusted Life Years (QALYs).

### Procedure

#### Assessment of eligibility informed consent and baseline assessment

Figure 1 provides an overview of the recruitment and study procedure. After informed consent is obtained eligibility is assessed during the baseline interview (T0) using the SCID I depression module, the IDS-C, and the MINI (modules bipolar disorder, psychotic disorder, alcohol and drug dependency). After randomization, the participant is informed about the condition to which he or she has been randomized. Also, the baseline questionnaires are administered at T0 (see Table 1).

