## Methods

### Design

Originally the study was designed as a single trial, randomizing patients who are in remission of depression over [a] continuation of medical treatment, [b] switching to MBCT, or [c] MBCT as an add-on to medical treatment. This protocol was approved by our ethical review board (CMO Arnhem-Nijmegen) and registered under number 2008/242. However, inclusion of patients was hampered by the fact that many patients turned out to have a strong treatment preference: some patients were eager to start with MBCT and other patients were reluctant to discontinue medical treatment. Continuing the trial as a trial with preference arms would have resulted in a substantial proportion of patients who would not have been randomly allocated to treatment, introducing a potential serious bias. We therefore decided to conduct two separate RCTs, one with patients who are reluctant to discontinue medical treatment, and one with patients who are particularly eager to try MBCT and at least not unwilling to discontinue medical treatment. In the former, patients are randomly allocated to either continuation of medical treatment, or continuation of medical treatment with MBCT as an add-on therapy (a parallel-group, randomized controlled superiority trial). In the latter, patients are allocated to either MBCT while continuing medical treatment, or to MBCT in combination with a tapering-off regimen of the medical treatment (a parallel-group, randomized controlled non-inferiority trial). In this way, we take optimal account of the patient preferences and the study population will be as representative as possible of patients seen in routine clinical practice. The change in protocol has been approved by the Medical Ethics Committee Arnhem-Nijmegen (20-02-2011). Here, we report the design of the two trials. See Figure 1 for a flow chart of the recruitment and study procedure.

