#### Randomization

Randomization is computerized using a minimization strategy while stratifying over the following variables: a) research centre, b) full versus partial remission (IDS-C score ≤ 11 versus > 11), c) number of depressive episodes in the past (3-4 versus ≥ 5), d) prior CBT (yes/no) and e) gender. Sub–threshold symptoms (partial remission) and number of past episodes are stratified because both are associated with relapse/recurrence risk [55]. Also, prior CBT is stratified because this has been shown to decrease relapse/recurrence risk [56]. Randomization is performed online by the research assistant who conducts the baseline assessment by entering the required information on a randomization website specifically designed for this study. The research assistant then communicates the treatment allocation to the patient, which means that he or she is no longer blind to the treatment condition. Unblinding of patients and research-assistants could not be avoided because the different conditions required different arrangements for treatment appointments, and separating this task from the assessments was logistically impossible in most research centers. To assess the reliability of the follow-up assessments, all interviews are audio taped and a random selection of actual, borderline or probable cases of relapse/recurrence is rated by an independent assistant blind to treatment allocation.

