##### Cost-effectiveness

Cost-effectiveness of mADM versus mADM + MBCT will be analyzed in trial 1 and cost-effectiveness of MBCT versus mADM + MBCT will be analyzed in trial 2. A non-parametric bootstrapping method will be used, performing 1000 replications of the original data to produce confidence intervals. Changes in health-related quality of life from baseline will be used to calculate QALYs in each group. Incremental cost-effectiveness will be expressed in terms of incremental costs per QALY gained. A cost-acceptability curve will be constructed for statistical analysis of the incremental cost-effectiveness ratio. In case of dominance a full cost analysis will be conducted to estimate the mean savings per patient per year. To estimate the long-term consequences of introducing MBCT in the prevention of relapse/recurrence, decision analytic modeling (TreeAge) will be used, comparing mADM, MBCT, and the combination of mADM and MBCT in patients with recurrent depression, over a period of 5 years. Estimates of costs, utilities, and probabilities will be derived from the trial (extrapolation) and, where available, the literature, or from experts. Sensitivity analyses will be conducted to explore sensitivity of the outcomes to various model assumptions.

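### The protocol article lists the T0 self-report questionnaires after randomisation and disclosure of the arm, and nowhere requires that they be completed first

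*Protocol article*

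**What the plan says.** In the protocol article, *Assessment of eligibility informed consent and baseline assessment* gives the steps in this order: consent, then eligibility at the baseline interview (T0) using the SCID-I depression module, the IDS-C and the MINI, and then: "After randomization, the participant is informed about the condition to which he or she has been randomized. Also, the baseline questionnaires are administered at T0".

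*Randomization* assigns these tasks to one person: "Randomization is performed online by the research assistant who conducts the baseline assessment". It continues: "The research assistant then communicates the treatment allocation to the patient". The same section accepts that patients and assistants are unblinded from that moment.

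Table 1 puts the interview instruments and the questionnaires in a single T0 column. The article refers to Figure 1 for the procedure, but that figure is not available here.

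On the use of the baseline, *Cost-effectiveness* (secondary analyses) says: "Changes in health-related quality of life from baseline will be used to calculate QALYs in each group".

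**The concern.** A baseline is useful in a randomised comparison because allocation cannot have influenced it. In an open trial, a self-report scale completed after the patient learns the arm loses that protection. Pleasure or disappointment can shift the score, and the shift can differ by arm. Taking change from such a baseline, or adjusting for it, then adds or removes a between-arm difference that treatment did not cause. The baseline cannot be collected again later.

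A reaction is plausible here. The study was redesigned because "many patients turned out to have a strong treatment preference". Within each trial the arms still differ in something patients may care about. In trial 1, controls are offered MBCT only after the study period. In trial 2, one arm tapers medication and the other continues it.

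**Working it through.** The plan gives no figure to reproduce. The check has three parts: the order of steps, the instruments exposed, and an illustration of size.

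**1. Order of steps.** Two readings fit the text.
- *Questionnaires before disclosure.* T0 is the eligibility interview, which must precede randomisation, and the questionnaires are placed at T0.
- *Questionnaires after disclosure.* The questionnaire sentence follows the disclosure sentence. One assistant could interview, randomise, disclose and hand out the forms in one visit, all of it labelled T0.

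Nothing in the available text excludes the second reading.

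**2. Instruments, if the second reading is followed.**

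| Instrument | Position | Exposed? |
|---|---|---|
| SCID-I, IDS-C, MINI | Eligibility interview, before randomisation | No |
| WHOQOL-bref, NEO-PI-R | T0 (Table 1), secondary outcomes | Yes |
| RRS, LEIDS, FFMQ, SCS | T0 (Table 1), process measures | Yes |
| EQ-5D | T0, and also T2 to T4 | Unclear |
| MAAS | Before each MBCT session | No T0 value |
| Adherence to MBCT | During the study | No T0 value |

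The EQ-5D is unclear because *Follow-up assessments* describes T2 to T4 as telephone contacts with an interview part only. It must therefore be given by interview at those visits, and it may be given that way at T0.

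*Mechanisms of change* restricts the mediation set to patients who attended at least 4 of 8 MBCT sessions. In trial 1 that leaves only the combination arm, so the mediation set has no between-arm contrast to distort.

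**3. Illustration for QALYs.** Let s be a between-arm shift in EQ-5D utility at T0 caused by disclosure and absent at later visits. The documents give no value, so s = 0.02 to 0.05 is assumed. Visits are at 0, 3, 6, 9, 12 and 15 months.
- Trapezoid weights in years: 0.125 at T0, 0.25 at each of T1 to T4, 0.125 at T5. Total: 0.125 + 4 × 0.25 + 0.125 = 1.25.
- *Area of change from baseline.* Change at T0 is zero by definition, and every later change is off by −s. Bias = −(1.25 − 0.125) × s = −1.125 × s. This gives 1.125 × 0.02 = 0.0225 and 1.125 × 0.05 = 0.05625, so about 0.023 to 0.056 in size, against the arm whose baseline was raised.
- *Plain area under the curve, no baseline adjustment.* Only the T0 value is wrong. Bias = +0.125 × s. This gives 0.125 × 0.02 = 0.0025 and 0.125 × 0.05 = 0.00625, so about 0.003 to 0.006.

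The quoted QALY sentence points to the first form but does not give the formula.

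**The case against.** The strongest reply is that the article never says the questionnaires follow disclosure. The reference to what happens after randomisation governs only the disclosure sentence. The word that opens the next sentence adds an item and does not mark a sequence, and T0 is tied to the pre-randomisation interview. Figure 1 might settle the order, and the order of forms within a visit is often left to the full protocol. This stands: a reader might infer that the plan prescribes post-disclosure baselines, and the text does not support that. What remains is that the article does describe the sequence, lists the questionnaires last, and contains no requirement to the contrary.

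Second, splitting the study by preference should dampen reactions. Both trial 1 arms keep the medication those patients are reluctant to stop, and both trial 2 arms receive the MBCT those patients want. That is fair. It makes a large reaction less likely but does not exclude one.

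Third, a reader might infer that every mediator is compromised. That is too wide: MBCT adherence and the MAAS have no T0 value, and the trial 1 mediation set has no between-arm contrast.

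Fourth, the stated use of these baselines is thin. Only QALYs are expressly taken as change from baseline, and the EQ-5D may have been part of the interview. The covariates named in *Primary analyses* are centre, baseline depressive symptoms and number of past episodes, none of which is a T0 questionnaire score. This limits the consequence. It does not remove it, because that section also admits other variables found to be uneven at baseline, and a questionnaire score could enter an adjusted analysis that way.

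**Conclusion.** The point holds as an ambiguity that the protocol should close. Its wording allows a site to collect the self-report baselines after the patient knows the arm. It does not show that any site does so or that any shift occurs.

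The measures at risk are the WHOQOL-bref, NEO-PI-R, RRS, LEIDS, FFMQ and SCS, and conditionally the EQ-5D. The QALY figures above rest on three assumptions: a shift of the assumed size, no persistence beyond T0, and an EQ-5D completed after disclosure. They also differ ninefold (1.125 against 0.125) between the two ways of computing QALYs, so they show why the order matters and are not an estimate of bias.

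A reader might also infer a threat to the main result. There is none to the relapse/recurrence outcome, which is assessed by SCID-I during follow-up and needs no T0 questionnaire, nor to the remission stratum, which uses the pre-randomisation IDS-C. Priority is therefore modest: the correction is worth making because it is nearly free and the loss cannot be repaired afterwards.

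**What to change.** In *Assessment of eligibility informed consent and baseline assessment*, state that all T0 questionnaires, including the EQ-5D, are completed before the assistant opens the randomisation website and before the patient is told the arm. Add a questionnaire completion-date field to that website, to be filled in before an allocation is returned.

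For patients already enrolled, record where known whether the T0 questionnaires came before or after disclosure. As a sensitivity analysis, repeat any change-from-baseline or baseline-adjusted analysis of self-report measures, including QALYs, without those who completed them after disclosure.

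The cost is a fixed order within the existing visit, one field on an existing web page and a short retrospective check. No extra visits or staff are needed. If sites already work in this order, one sentence settles the point.
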